# SUMMARY

The South Africa National Department of Health (NDOH) intends to launch its newly developed National Adherence Guidelines for Chronic Diseases (HIV, TB and NCDs) throughout South Africa in the coming year. Early implementation of the “minimum package” of interventions described in the Adherence Guidelines for HIV patients will take place at 12 primary health clinics and community health centres in four provinces starting in July 2015. To maximize the learning potential of this early implementation stage, NDOH will match the intervention clinics with 12 comparison clinics and randomly allocate intervention or comparison status within the pairs of clinics. This will allow the outcomes of the interventions to be evaluated using a cluster-randomized design and generate data on the costs of implementation and the potential need for adherence support for the other diseases addressed in the guidelines (tuberculosis, hypertension, and diabetes). This protocol is for the evaluation, which will generate information on the effectiveness of minimum package interventions and help improve the design, implementation, and budgeting of the guidelines.

We will assess the effectiveness of five interventions in the minimum package: 1) Fast track initiation counseling for patients eligible for antiretroviral therapy; 2) Enhanced adherence counseling for unstable patients on HIV treatment; 3) adherence clubs for stable patients on HIV treatment; 4) decentralized medication delivery for stable patients on HIV treatment; and 5) early tracing of all patients who miss an appointment by two weeks. We will also estimate for each study site an overall “adherence guideline impact” to provide an indication of the effectiveness of the package as a whole.

In addition, we will estimate the cost of each of the interventions listed above compared to standard of care. Finally, we will describe the cascade of care for tuberculosis, hypertension, and diabetes, three other chronic diseases for which little information currently exists. To evaluate these interventions we will work with the National Department of Health (which will implement the interventions) to randomize 24 clinics in 4 provinces 1:1 to receive the interventions or continue standard of care. All evaluations will use data routinely collected by the clinics, with no study interaction with subjects. A total of 8,256 patients will be enrolled and followed for up to 20 months to estimate short- and long-term outcomes.

# BACKGROUND, RATIONALE, AND OBJECTIVES

## **a. Background**

For antiretroviral therapy (ART) for HIV and treatment for other chronic diseases to be effective, patients must remain in care for long periods of time, initiate treatment as early as allowed under prevailing guidelines, consistently achieve high levels of adherence to their treatment regimen and, as a result, exhibit low and stable monitoring test results and/or treatment completion. In the case of HIV, treatment is lifelong and requires consistent, nearly complete adherence to sustain an undetectable viral load. Consistent adherence is also necessary to achieve success with treatment for tuberculosis, diabetes, hypertension, and other non-communicable diseases (NCDs). Numerous studies and reviews[1–4], as well as the South African National Department of Health’s (NDOH) own data[5], have indicated that retention in care and adherence to ART in South Africa are sub-optimal and pose a serious threat to the long-term success of the national HIV response. Although there is less evidence on hand, these same problems almost certainly also pertain to tuberculosis (TB), for which treatment completion and cure rates do not approach global targets[6], and to NCDs, for which almost no treatment adherence data are available.

To address this challenge, in 2014 the NDOH developed the “National Adherence Guidelines for Chronic Diseases (HIV, TB and NCDs)”. The guidelines address the provision of a minimum package of interventions to increase linkage to care, retention in care, and adherence to treatment. The minimum package interventions are listed in Table 1.

**Table 1. National Adherence Guidelines minimum package of interventions**

| **Approach** | **Intervention** |
| --- | --- |
| Education and counselling | 1. Fast track initiation counseling* 2. Enhanced adherence counseling for unstable patients* 3. Child disclosure counseling for children living with HIV |
| Repeat prescription collection strategies | 1. Adherence clubs* 2. Spaced and fast lane appointment systems 3. Decentralised medication delivery* |
| Patient tracing | 1. Early tracing of all missed appointments* |
| Integrated HIV, TB, NCD care | 1. Integrated consultation and counselling |

*Indicates interventions included in this evaluation

## **b. Rationale**

Although there is some published or unpublished evidence of the effectiveness of each of these interventions for HIV care[7–9], most have not been implemented jointly or at scale, nor have they been evaluated as delivered routinely by public sector facilities, without external technical assistance or resource support. South Africa also lacks evidence on HIV/NCD co-morbidities and on the prevalence and current treatment outcomes of patients presenting with NCDs. Better information is needed to guide the NDOH’s rollout of the minimum package at national scale and about the number of patients requiring intervention and the cost of delivering the interventions to them.

Prior to national scale-up of the Adherence Guidelines, NDOH intends to select 12 clinics (primary health care clinics and community health centres) for early implementation of the minimum package for HIV patients. This will generate information to refine the guidelines, gain experience in implementation, and project budgetary needs. To maximize the learning potential of these early implementation sites, they will be matched with 12 other clinics and then one clinic in each pair will be randomly assigned to receive the interventions, with the other clinic in the pair serving as a comparison site. This will allow for a cluster-randomized evaluation of the impact of the interventions. The early implementation sites will also generate data on the costs of the interventions and on how to tailor and target the interventions to tuberculosis, hypertension, and diabetes. At the request of the NDOH, we previously developed a set of cost estimates for national implementation of the Adherence Guidelines using published sources of data[16]; this evaluation will also allow refinement of the cost estimates, which are needed to assure sufficient resources for large-scale delivery.

Each of the interventions listed in Table 1 addresses a unique population of patients within a clinic, with the exception of interventions 4-6, which are substitutes for one another. For example, fast track initiation counseling is limited to patients eligible to start treatment; enhanced adherence counseling is limited to patients failing treatment; early tracing of missed appointments is limited to patients who are late for scheduled visits; and so on. While individual patients may become eligible for multiple interventions over the course of their care, the interventions will not serve overlapping cohorts of patients simultaneously. This will allow the impact of each intervention to be evaluated separately, as well as within the overall package.

## **c. Objectives**

The overall aims of this study are to assess the impact of a subset of the National Adherence Guidelines’ minimum package of interventions on HIV patients’ treatment outcomes at public sector clinics; estimate the costs of the interventions; and describe the cascade of care for TB, hypertension, and diabetes at these same clinics. All implementation of the interventions and generation of data will be done by NDOH; this protocol, which has been developed in partnership with the National Department of Health, is solely for the analysis of routinely collected data.

The specific objectives of the evaluation are to:

*Objective 1: Among HIV-infected patients newly eligible for antiretroviral therapy,* ***evaluate the impact of Fast Track Treatment Initiation Counselling on initiation and viral suppression****.*

Research questions:

- What is the effect of Fast Track Initiation Counselling on rates of initiating ART within 30 days of determining ART eligibility?
- What is the effect of Fast Track Initiation Counselling on rates of being alive, in care, and virally suppressed within 9 months of determining ART eligibility?

*Objective 2: Among HIV-infected patients who are stable on antiretroviral therapy,* ***evaluate the impact of Adherence Clubs on ART adherence and viral suppression****.*

Research questions:

- What is the effect of Adherence Clubs on medication possession over the first 3 months of intervention eligibility compared to standard of care?
- What is the effect of Adherence Clubs on rates of viral suppression within 12 months of intervention eligibility compared to standard of care?

*Objective 3: Among HIV-infected patients who are stable on antiretroviral therapy,* ***evaluate the impact of Decentralized Medication Delivery on ART adherence and viral suppression****.*

Research questions:

- What is the effect of Decentralized Medication Delivery on medication possession in the first 3 months after intervention eligibility compared to standard of care?
- What is the effect of Decentralized Medication Delivery on rates of viral suppression within 12 months of intervention eligibility compared to standard of care?

*Objective 4: Among HIV-infected patients who have poor adherence to antiretroviral therapy,* ***evaluate the impact of Enhanced Adherence Counselling on treatment adherence and viral suppression****.*

Research question:

- What is the effect of Enhanced Adherence Counselling on rates of being alive, in care, and virally suppressed within 3 and 12 months of intervention eligibility?

*Objective 5: Among HIV-infected patients in antiretroviral therapy programs who miss a scheduled appointment by 5 days,* ***evaluate the impact of Early Patient Tracing on retention in care****.*

Research questions:

- What is the effect of Early Patient Tracing on rates of returning to care by 3 and 12 months of tracing?
- What is the effect of Early Patient Tracing on rates of remaining in care by 12 months of tracing?

*Objective 6: For each clinic included in the study,* ***evaluate the overall impact of the Adherence Guidelines on patient outcomes****.*

Research questions:

- What is the effect of the package of interventions on patient retention in care overall?
- What is the proportion of population in need expected to benefit from the package of interventions?

*Objective 7:* ***Estimate the incremental and total cost of each of the interventions*** *listed above compared to standard of care.*

Research questions:

- What is the average cost per patient reached with the intervention?
- What is the average cost per successful outcome achieved?

*Objective 8:* ***Describe the current status of the cascade of care and adherence to treatment for tuberculosis, hypertension, and diabete****s, for the purpose of tailoring the minimum package of interventions to these conditions in the national rollout.*

Research questions:

- What is the prevalence of previously and newly diagnosed TB, hypertension, and diabetes among the population of patients presenting for care at primary health clinics, stratified by age, sex, and HIV status where possible?
- What proportion of diagnosed cases of these conditions are initiated on guideline-compliant treatment?
- What proportion of cases have satisfactory outcomes, based on current guidelines 12 months after diagnosis?
- For each condition, what proportion of patients are lost to care or discontinue treatment during the first 12 months after diagnosis?

Note that the impacts being assessed under Objectives 1-6 are the impacts of the interventions as implemented in the early phase of the national rollout of the guidelines. As is the case with program evaluations in general, results will reflect both intervention efficacy and implementation quality, which may in turn reflect the early learning stage of national policy implementation.

Prior to starting data collection for this evaluation, we will develop descriptions of each study facility. This will include staffing, patient population, services provided, current standard of care, existing adherence-related services and programs, quality of routine data collection, support received from PEPFAR and other external partners, community organizations that refer to the clinic or support its patients, relevant published studies already completed at the sites, and other facility-level information that may help interpret the evaluation results and inform recommendations. These preparatory descriptions are not an objective of the evaluation itself and do not involve human subjects, but will provide useful insights as to the readiness of sites for implementation, challenges and gaps that need to be addressed and the implications of these on the implementation and scale-up of national guidelines.

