## **b. Inclusion and Exclusion Criteria**

For Objectives 1-5 and Objective 8, we will enroll a specific cohort of patients. These will be numbered in accordance with the objective number for Objectives 1-5; for Objective 8, the cohort will be called the “TBHD cohort”, in reference to tuberculosis, hypertension, and diabetes. This TBHD cohort will be made up of patients who have been screened for TBHD (50%) and patients who are newly diagnosed with TB, hypertension or diabetes (50%). For all cohorts, inclusion and exclusion criteria are as shown below. For Objectives 1-5, these criteria follow the December 2014 national guidelines for HIV care and ART[10] and November 2015 National Adherence Guidelines for Chronic Disease (HIV, TB and NCDs) [11].

*Cohorts 1-5 and TBHD cohort inclusion criteria*

- ≥ 18 years old
- Meet the inclusion criteria for one or more of Cohorts 1-8

*Cohorts 1-5 and TBHD cohort exclusion criteria*

- Not resident in the facility’s catchment area
- Recorded intention to transfer care to a different facility within 12 months
- Pregnant and eligible for PMTCT

*Objective 1/Cohort 1 inclusion criteria (Patients newly eligible for ART—fast track treatment initiation)*

- Determined to be eligible to start ART under prevailing national guidelines (CD4 count < 500, WHO Stage 3 or 4 condition, TB, cryptococcal meningitis)

*Objectives 2 and 3/Cohorts 2 and 3 inclusion criteria (Patients stable on ART—adherence clubs or decentralized medication delivery)*

- On same ART treatment regimen for at least 12 months
- Most recent viral load taken in past 6 months
- Two consecutive viral loads undetectable (<400 copies/ml^3^)

*Objective 4/Cohort 4 inclusion criteria (Patients on ART with poor adherence—enhanced adherence counseling)*

- On first line ART for at least 6 months
- Poor adherence as indicated by an elevated viral load (>400 copies/ml^3^)

*Objective 5/Cohort 5 inclusion criteria (Patients lost from ART programs—early patient tracing)*

- Initiated ART
- Fail to return for a scheduled appointment within 5 to 90 days from their appointment date

*Objective 8/TBHD cohort inclusion criteria (Tuberculosis, hypertension, and diabetes patients)*

- Screened for or diagnosed with for TB or hypertension within the last month, or diabetes within last 6 months

*Objective 8/TBHD cohort exclusion criteria (Tuberculosis, hypertension, and diabetes patients)*

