# DATA ANALYSIS

## **a. Outcomes**

Table 3 lists the primary and secondary outcomes we will measure for each of the objectives. Each primary outcome includes both a short term (S) outcome and a longer term (L) outcome for assessment of the immediate and longer term outcomes of the intervention. Our ability to assess secondary outcomes will depend on data availability and duration of follow up. Note that viral suppression in the current South African ART guidelines is defined as viral load below 400 copies/ml^3^, and this is the threshold that the National Health Laboratory Service will report, and is therefore what we will use.

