**Table 3. Evaluation outcomes**

| **Objective** | **Primary Outcome** | **Secondary outcomes** |
| --- | --- | --- |
| Fast track ART initiation counseling (Objective 1) | Proportion of patients who initiate ART within 30 days of becoming ART eligible (S) and the proportion of patients who are alive, in care, and virally suppressed (< 400 copies/ml^3^) within nine months of ART eligibility (L). | Proportion of patients who initiate ART within one week of becoming ART eligible  Demographic and clinical characteristics of patients who do and do not achieve primary outcomes (age, sex, baseline CD4 counts, TB diagnosis, other characteristics as allowed by data). |
| Adherence clubs (Objective 2) | Proportion of patients eligible for participation in an adherence club who receive all medications within the first four months after club eligibility (S) and the proportion virally suppressed (< 400 copies/ml^3^) at twelve months after club eligibility (L). | Proportion of patients consistently participating in club  Demographic and clinical characteristics of patients who do and do not achieve primary outcomes. |
| Decentralized medication delivery (Objective 3) | Proportion of patients eligible for decentralized medication delivery who receive all medications within the first three (S) months after delivery eligibility and viral suppression (< 400 copies/ml^3^) twelve months after delivery eligibility (L). | Proportion of patients consistently receiving medications  Demographic and clinical characteristics of patients who do and do not achieve primary outcomes. |
| Enhanced adherence counseling (Objective 4) | Proportion of patients with an elevated viral load who are alive, retained in care and resuppress their viral load (< 400copies/ml^3^) within three (S) and twelve months (L) of eligibility for enhanced adherence counseling. | Demographic and clinical characteristics of patients who do and do not achieve primary outcomes. |
| Early tracing of patients lost to follow up (Objective 5) | Proportion of patients eligible for early patient tracing who return to care within three (S) and twelve (L) months of eligibility. | Proportion of patients reached by tracers  Number of tracing attempts required; proportion of patients retained in care for at least one additional routine visit after tracing  Demographic and clinical characteristics of patients who do and do not achieve primary outcomes. |

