| Overall impact (Objective 6) | Proportion of population in need at each clinic who achieve the short term primary outcomes defined above. | Proportion of population in need at each clinic who achieve the long term primary outcomes defined above. |
| Cost  (Objective 7) | Average cost per patient receiving an adherence intervention | Average cost per primary outcome achieved; average cost per 1000 patients receiving the observed mix of interventions |
| TB, hypertension, and diabetes (Objective 8) | For each condition, proportion of patients eligible for treatment who have 80% visit compliance in the first three months after diagnosis (S) and who achieve disease control at the six-month visit after diagnosis (L) as indicated in “Primary Care 101,” the NDOH’s guide for primary health clinic services[15]. The six-month visit will be represented by the visit closest to six months within the window of 5-8 months after diagnosis. The disease control indicators to be measured, with page references for Primary Care 101, are:  TB: cured or treatment completed indicated as the patient’s status at 6 months (page 57)  Hypertension: blood pressure controlled at 6-month visit, with control defined as < 140/90 (or 120/70–140/80 if diabetes, or <130/80 if CVD, heart failure or kidney disease) (page 74)  Diabetes: random glucose < 8 or HbA1c ≤ 7% at 6 month visit (page 71) | Among patients screened, prevalence of pre-diabetes elevated blood sugar (defined by Primary Care 101 as random glucose between 7.8 and 11) and pre-hypertension elevated blood pressure that require monitoring  Proportion of patients diagnosed with pre-diabetes or pre-hypertension who a) progress to diabetes and hypertension; or b) remain in care and receive appropriate monitoring for their condition over 12 months  Prevalence of diabetes, hypertension and TB among patients screened  Proportion of diagnosed patients initiated on appropriate treatment  Proportion of patients on treatment retained in care at 12 months. Loss to follow up will be defined as being 30 days late for a scheduled appointment.  Demographic and clinical characteristics of patients who do and do not achieve primary outcomes. |

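### Objectives 2 and 3 give the long-term viral-suppression outcome two incompatible time definitions: within 12 months of eligibility, and at 12 months

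*Protocol*

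**What the plan says.** - Section 3.c, Objective 2: "What is the effect of Adherence Clubs on rates of viral suppression within 12 months of intervention eligibility compared to standard of care".
- Section 3.c, Objective 3: "What is the effect of Decentralized Medication Delivery on rates of viral suppression within 12 months of intervention eligibility compared to standard of care".
- Table 3 (section 10.a), Objective 2: the proportion suppressed "at twelve months after club eligibility (L").
- Table 3, Objective 3: suppression "twelve months after delivery eligibility (L").
- Section 10.a on the status of these outcomes: "Each primary outcome includes both a short term (S) outcome and a longer term (L) outcome". The 12-month result is therefore part of the primary outcome.
- Section 8.b, entry to Cohorts 2 and 3: "Two consecutive viral loads undetectable" (below 400 copies), the latest taken in the past 6 months. Section 10.a uses the same 400-copy threshold for the outcome. Sections 4.b and 4.c also admit patients whose stability a clinician confirms.
- Section 9.c: follow-up by record review lasts at least 14 months, including two months beyond the year so that one-year outcomes can occur.
- Table 3, Objective 8, for comparison: "The six-month visit will be represented by the visit closest to six months within the window of 5-8 months after diagnosis".

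**The concern.** Suppression within a period and suppression at a time point are different outcomes. Under the period wording, on its most natural scoring, one suppressed result at any time in the year is enough. Under the time-point wording, the patient's status about a year after eligibility decides.

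In a cohort that starts unsuppressed the two may lie close together. Here they do not, because most patients are suppressed on entry and an adherence intervention for them can only maintain suppression. A cumulative definition does not register the event of interest, which is loss of suppression.

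The choice affects the relative risk planned in section 10.c for two of the five interventions. It also affects the secondary outcome of Objective 6, which uses the long-term outcomes, and the cost per primary outcome achieved under Objective 7. With both wordings in the protocol, the definition could be settled after results are seen.

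**Working it through.** **1. The wordings side by side.**

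| | Section 3.c | Table 3 |
|---|---|---|
| Objective 2 | within 12 months of eligibility | at twelve months after eligibility |
| Objective 3 | within 12 months of eligibility | twelve months after eligibility |
| Objective 4 | within 3 and 12 months | within three and twelve months |

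Table 3 uses the word 'at' only for Objective 2, but the Objective 3 wording has the same sense. For Objective 4 both places use the period wording: Table 3 reads "within three (S) and twelve months (L) of eligibility for enhanced adherence counseling". So the protocol uses 'within' where it means a period, and the different wording for Objectives 2 and 3 cannot be dismissed as loose style.

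**2. One patient, two scores.** Take a patient with a result below 400 soon after eligibility and a result above 400 at month 12. Read as any suppressed result in the period, section 3.c counts a success. Table 3 counts a failure. Neither place says that the qualifying result must come after eligibility, so on a literal reading it is not even clear that the entry result is excluded.

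**3. Effect on the contrast (illustration only).** The protocol gives no 12-month suppression rate, number of tests per patient or correlation between tests, so everything in this step is assumed: two tests after eligibility, the same suppression probability p at each, and correlation r between them.

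P(at least one suppressed) = 1 − [(1 − p)² + r·p·(1 − p)]

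For p = 0.80 and r = 0: 1 − 0.04 = 0.960. For p = 0.80 and r = 0.5: 1 − (0.04 + 0.08) = 0.880. The other entries follow in the same way.

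| Single-test contrast | r | Any-of-two contrast | Difference | RR |
|---|---|---|---|---|
| 80% vs 90% (10 points, RR 1.125) | 0 | 96.0% vs 99.0% | 3.0 points | 1.03 |
| | 0.5 | 88.0% vs 94.5% | 6.5 points | 1.07 |
| | 0.8 | 83.2% vs 91.8% | 8.6 points | 1.10 |
| 85% vs 95% (10 points, RR 1.118) | 0 | 97.75% vs 99.75% | 2.0 points | 1.02 |
| | 0.5 | 91.4% vs 97.4% | 6.0 points | 1.07 |

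The contrast shrinks in every row. The shrinkage depends heavily on r and disappears as r approaches 1.

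**4. What the follow-up allows.** Every patient is followed for at least 14 months, that is 14 − 12 = 2 months past the time point. A window symmetric about month 12 and observable for everyone can therefore run at most from month 12 − 2 = 10 to month 14.

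**5. What is not affected.** Section 10.b bases each sample size on the short-term outcome, so no stated sample size or power figure depends on this definition.

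**The case against.** The strongest reply is that Table 3 is the operative definition: section 10.a introduces it as the list of outcomes to be measured, whereas section 3.c holds broad research questions. Much of this stands, and it is why the fix follows Table 3. But the protocol gives no order of precedence, and the research question is what a report would be held to answer.

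Three further replies stand:

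- **Window.** Which viral load counts, and in what window, is commonly left to the SAP, which was not available here. The absence of a window is not an error by itself, even though Objective 8 has one. A SAP can add a window, but it cannot satisfy both time definitions.
- **Ceiling.** A reader might infer that under the period wording nearly every patient succeeds. The documents do not support that. No rate is given, clinician-confirmed patients need not have two documented suppressed results, and if untested patients count as failures the tested fraction caps the outcome. For example, assuming 80% tested and 95% of those suppressed gives 0.80 × 0.95 = 76%.
- **Test timing by arm.** A reader might also infer that clubs and decentralized delivery shift testing dates in one arm. Section 4 assumes that all sites follow the same national care guidelines, and no comparison-arm visit or viral-load schedule is given, so this remains speculation.

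Nor does the point extend to Objective 4. Its wording is consistent, and its outcome also requires being alive and retained in care. Preferring a late viral load there would be a design preference.

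**Conclusion.** The point holds for Objectives 2 and 3. One long-term primary outcome has two incompatible time definitions, affecting two cohorts of 576 planned patients each (2 × 576 = 1,152). The contradiction rests on the text alone and needs no assumption.

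That the period wording would hide rebound and weaken the contrast rests on two things: reading it as any suppressed result, and the largely suppressed entry population. The direction is then clear. The size cannot be calculated from the documents, and the figures above only show that it could range from slight to most of the effect. The wording should be settled before any outcome data are analysed.

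**What to change.** 1. In section 3.c, change the long-term questions for Objectives 2 and 3 to the Table 3 time point.
2. In both places, define the outcome as suppression (below 400) on the post-eligibility viral load closest to 12 months, within one pre-specified window centred near month 12 and ending no later than month 14. Objective 8 already handles its six-month visit this way. A window reaching back to month 6 would not serve, because a half-year result would then pass as twelve-month suppression.
3. Apply the rule identically in both arms.
4. State how patients without a result in the window are counted, including those who died, transferred or were lost. Unlike Objectives 1 and 4, this outcome does not require being alive and in care. Counting untested patients as failures makes the outcome partly a measure of testing, so report the proportion tested by arm whichever rule is chosen.

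The cost is a wording change in two places. No extra tests are needed, since section 9.b already collects the dates and results of all viral loads. The downside is that some patients will have no routine result in the window, and the suppression percentages may look lower than under the period wording.
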